### *Sample size*

Since the study is a pilot, 50 patients are intended to be recruited to participate in the randomized control trial. Sample size calculations will be made during the study, based on gathered data. If feasible, more than 50 patients may be enrolled in order to get sufficient statistical power.

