### *Randomization (sequence generation)*

Using statistical software, a statistician will generate a blocked randomization list that will be used to allocate patients to either the intervention or the control group. Blocks of four will be used.

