### *Compliance with treatments (secondary outcome)*

Compliance with pharmacotherapy in the last week will be evaluated. An interview questionnaire based on the 2003 Asthma Consensus Conference guidelines (36) and adapted to the 2012 Asthma Consensus Conference guidelines (3) will be administered at baseline and after a 2-month follow-up. It has already been used to describe the appropriate use of asthma drugs among patients with moderate to severe asthma (19). The questionnaire is composed of a set of 11 hierarchical criteria; there were originally 12, but one of them is not relevant anymore. The set of criteria evaluates, in the last week, the use and the frequency of use of controller/rescue medication, and add-on therapy (if relevant). In order to be classified as compliant, patients need to meet all the 11 criteria (19), which set patients who are very compliant apart from others (37).

The questionnaire also allows compliance to maintenance/rescue/add-on medication to be expressed as a percent score ( $[\text{doses taken}/\text{doses prescribed}] \times 100$ ). In that case, a score that is  $\geq 80\%$  but  $\leq 100\%$  is indicative of compliance (38). The variable will nevertheless be analysed as a continuous one.

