### *Data analysis*

Descriptive analyses will be performed in order to describe the study population: continuous variables will be described as means or medians, depending on normality of distributions, and categorical variables as proportions.

Generalised linear models will be used to compare the intervention and control groups on the dependent variables (41). For asthma knowledge, decisional conflict, compliance with maintenance/rescue/add-on pharmacotherapy, and asthma control, a normal distribution and an identity link will be used, since all 4 variables are expressed as continuous ones. Assumptions of normality, and homoscedasticity will also be checked. A log transformation could be used to correct departure from normality, if relevant. For compliance with pharmacotherapy, a binomial distribution and a log link will be used as this variable is expressed as a binary one. In models, effects for group (intervention and control), time (baseline and 2-month follow-up) and group-by-time interaction will be included. The effect of the shared decision making aids on health outcomes will then be estimated by the interaction term between the group and time. Mean differences (continuous variables) and prevalence ratios (dichotomous variable) have been

chosen as effect measures. In addition, generalized estimating equations will be used in order to take repeated measures into account.

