If covariates (asthma knowledge, age, body mass index, atopy, environmental triggers, and respiratory tract infections) are not distributed evenly between groups, we will adjust for them in analyses. Predictors of health outcomes will be incorporated into the model as confounders if they result in a >10% change in the effect measure, following a descending procedure. Exploratory subgroup analyses according to asthma severity will be conducted since pharmacotherapy and compliance with treatments are getting more complex with the severity of the disease. Statistical interaction of body mass index will also be exploratory assessed since this covariate is hypothesized to modify the effectiveness of intervention aiming at improving asthma control (42). In addition, exploratory statistical interaction of age, education and length of the patient's meeting with the asthma nurse will be evaluated since we hypothesize that the effect measure may vary according to the level of measurement of these variables. Regarding adherence to medication, sensitivity analyses will be carried out according to different cut-offs, that will range from 60 to 80% of inhaled prescribed doses.

SAS version 9.3 (SAS Institute Inc., Cary, USA) will be used to perform the statistical analyses, using PROC GENMOD. A 2-tailed *p*-value less than 0.05 will be considered indicative of statistical significance. Since the study is a pilot, power calculation will be made *a posteriori*. Alternatively, the study size is based on the number of patients that may realistically be recruited at the IUCPQ Research Center or Outpatient Asthma Clinic according to the timeframe. Nevertheless, sample size calculations will be made during the study, based on gathered data. If feasible, more patients may be enrolled in order to get sufficient statistical power.

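### Binary compliance (all 11 criteria met) is analysed by a log-link GEE interaction in about 25 patients per arm; one empty group-by-visit cell makes the prevalence ratio non-estimable and can make a sandwich-based Wald p-value spuriously extreme

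*Protocol*

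**What the plan says.** The Data analysis section fixes the model for the binary outcome: "For compliance with pharmacotherapy, a binomial distribution and a log link will be used as this variable is expressed as a binary one". It adds that "generalized estimating equations will be used in order to take repeated measures into account", and that the effect of the aids is "estimated by the interaction term between the group and time". The software is PROC GENMOD and a two-tailed "value less than 0.05 will be considered indicative of statistical significance". Annexe 1, Table 6 repeats the binomial distribution and log link for this outcome. Its footnotes promise a prevalence ratio, a 95% confidence interval and the p-value of the interaction.

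The outcome is strict. Under Compliance with treatments: "In order to be classified as compliant, patients need to meet all the 11 criteria". The protocol presents this rule as one that separates highly compliant patients from the rest.

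The trial is small: "Since the study is a pilot, 50 patients are intended to be recruited to participate in the randomized control trial", with "Blocks of four will be used" for two groups. The Data analysis section also plans severity subgroups and gives compliance as a reason: "Exploratory subgroup analyses according to asthma severity will be conducted since pharmacotherapy and compliance with treatments are getting more complex".

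The protocol names neither the test statistic nor the type of standard error. It gives no expected compliance rate.

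**The concern.** An all-or-nothing rule over 11 criteria, about 25 patients per arm and four group-by-visit cells make small counts foreseeable. On the log scale a cell with no compliant patient has no finite estimate. The robust variance of that estimate does not grow with it, so a Wald ratio of the two can become as large as the fitting routine allows. The test then rejects because a cell is empty, not because the arms differ. This includes a cell that is empty at baseline, before any aid has been used. At stake is a false claim of effect, or no usable result at all, on a named secondary objective.

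**Working it through.** There is no stated figure to reproduce, since the protocol gives neither a power calculation nor a rate for this outcome.

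**Inputs from the protocol:** 50 patients, two groups, binomial distribution with log link, GEE, group-by-time interaction, two-tailed 0.05.

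**Assumptions:** 1:1 allocation (25 per arm), no dropout, no covariates, the same prevalence in all four cells (no effect), within-patient correlation 0.3 to 0.5, Wald test on sandwich errors.

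**1. What an empty cell does.** With two complete visits and no covariates the model is saturated, so:

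- Interaction: b = [ln p(I,2) − ln p(I,1)] − [ln p(C,2) − ln p(C,1)].
- Sandwich variance per arm: (1−p1)/(n·p1) + (1−p2)/(n·p2) − 2(p12 − p1·p2)/(n·p1·p2), where p12 is the proportion compliant at both visits.
- In an empty cell the fitted mean μ goes to 0 and ln μ to minus infinity. Its sandwich variance is n·μ²/(n·μ)² = 1/n = 0.04, however far the estimate has run. Its covariance with the other visit is zero.

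The working correlation changes neither the estimate nor this variance.

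**2. A worked table.** Compliant patients out of 25 at baseline and 2 months: intervention 0 and 2, control 2 and 2, with no control patient compliant at both visits.

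- Intervention variance: 0.04 + 0.92/(25 × 0.08) = 0.04 + 0.46 = 0.50.
- Control variance: 0.46 + 0.46 + 2 × 0.0064/(25 × 0.0064) = 0.92 + 0.08 = 1.00.
- SE = √1.50 = 1.225.
- The coefficient moves about one unit per iteration: 5.29 after 5 iterations (z = 4.3, p = 1.6e-05) and 12.29 after 12 (z = 10.0, p = 1e-23).
- Fisher's exact test at 2 months (2/25 against 2/25): p = 1.00.
- With model-based errors the SE at iteration 12 is 329 and p = 0.97.

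A second table, intervention 2 then 3 and control 2 then 0, gave p = 6e-97 in an independence GEE, against Fisher p = 0.23.

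**3. How often this happens with no effect.** With zero correlation, P(at least one empty cell) = 1 − [1 − (1−p)^25]^4. At p = 0.10, 0.9^25 = 0.072 and 1 − 0.928^4 = 26%. Simulation at correlation 0.3 to 0.5 (100,000 trials per setting, diverging log mean stopped at −20) gave:

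| Patients per arm | Prevalence | At least one empty cell | False-positive rate |
|---|---|---|---|
| 25 | 5% | 65–69% | 42–50% |
| 25 | 8% | 37–39% | 28–33% |
| 25 | 10% | 23–25% | 20–23% |
| 25 | 15% | 6–7% | 8–9% |
| 25 | 20% | 1.5% | about 5% |
| 8 (assumed severity subgroup, 25/3) | 20% | 46–49% | 33–39% |
| 8 | 30% | 19–20% | 17–19% |

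With exactly one empty cell, rejection was 100%. In the 25-per-arm trials with no empty cell it was at most 4.9%. The excess therefore comes only from empty cells.

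**4. Alternatives with no effect, 25 per arm.**

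- Fisher's exact test at 2 months rejected in 0.0–3.1% of trials (prevalence 4% to 40%, correlation 0 to 0.6).
- An exact permutation test of change rejected in 0.0–3.1% over the same range.
- A generalised score test of the same GEE interaction rejected in 1.3–1.7% at 5% prevalence, 3.5–4.8% at 10% and 3.9–5.5% at 20% (correlation 0.3 and 0.5).

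**5. Power.** With prevalence 10–40% rising to 40–75% under the aids, Fisher's test at 2 months had about 51–66% power, against 31–53% for the interaction Wald test.

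**The case against.** The strongest reply is that the Wald test on sandwich errors is an inference. A reader might infer that the protocol prescribes it. It does not: it promises only a confidence interval and a p-value for the interaction. The choice decides the result, because a score test of the same model keeps its level and model-based errors fail in the opposite direction, with p near 1. This stands as a limit on the false-positive figures. It does not rescue the planned effect measure, because with one empty cell the prevalence ratio has no finite estimate under any of these choices.

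Second, test statistics and fallback rules are often left to a statistical analysis plan. That is fair, and their absence alone would be no finding. Here, however, the protocol itself fixes the link, the effect measure, the interaction, the software and the form of reporting, and these lead to the problem.

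Third, prevalence is unknown. Multiplying 11 independent pass rates of 0.80, 0.85 or 0.90 would give 9%, 17% or 31%, but the protocol calls the criteria hierarchical and applies the add-on ones only where relevant. Independence is not supported, and the true rate could be higher. This stands.

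Fourth, it is tempting to read the chance of an empty cell (65–69% at 5% prevalence) as the false-positive rate. That overstates it, because two empty cells in one arm or at one visit can cancel in the interaction.

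Finally, this is one secondary outcome of a pilot, compliance is also analysed as a percentage score, the severity subgroups are exploratory, and Table 6 would show an empty cell. All true. A reader might also infer from Research Utility that implementation would hang on this result, but that section speaks of health outcomes in general.

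**Conclusion.** The concern holds in a conditional form. What follows from the protocol's own choices is that one empty group-by-visit cell leaves the planned prevalence ratio non-estimable. If the p-value is a Wald test on sandwich errors, such a table is declared significant with no effect present. The false-positive rate is then several times nominal at a prevalence of about 10% or less, modestly raised at 15% and nominal at 20% or more. The severity subgroups are still affected at 20–30%.

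These sizes rest on assumed prevalence, correlation, 1:1 allocation and complete follow-up, and the subgroup figures on an equal split by severity. GENMOD itself was not run, so where its iterations would stop, and hence the exact p-value, is untested. The documents do not support saying that the trial will report a false effect. They do show a stated method that can fail badly in a foreseeable situation, and the replacement is cheap, so the change should be made.

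**What to change.** In Data analysis and in the binary compliance row of Table 6:

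- Base the test on the 2-month proportions, using Fisher's or an unconditional exact test, with a score-based 95% CI for the prevalence ratio or the risk difference. Alternatively, keep the GEE interaction but test it with a score or permutation test.
- State that the log-link GEE Wald p-value and CI are not reported when any group-by-visit cell has no compliant patient.
- In the severity subgroups, show counts only for this outcome.

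The cost is a few sentences and one table row. The exact test is somewhat conservative and does not use baseline compliance; on the power figures above, that loss is small. The score or permutation route retains the baseline information.

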### *Decisional conflict (primary outcome)*

Decisional conflict will be assessed through a French version of OHRI Decisional Conflict Scale (18). The questionnaire will be filled at baseline and after a 2-month follow-up. Sixteen items evaluate 5 dimensions of decisional conflict (informed, values clarity, support, uncertainty, effective decision) using a Likert scale. Patients' responses range from 0 (strongly agree) to 4 (strongly disagree). Patients' responses are summed, divided by 16, and multiplied by 25. Consequently, the decisional conflict score ranges from 0 (low decisional conflict) to 100 (high decisional conflict). A score greater than 37.5 suggests that there is a meaningful decisional conflict, but a score that is less than 25 is not associated with it (33). The variable will nevertheless be analysed as a continuous one. The reliability of the OHRI Decisional Conflict Scale (English low literacy version) has been evaluated using a Cronbach's  $\alpha$ , which value was above the 0.7 threshold (34). Test-retest coefficient also supports its reliability (35). The scale has been shown responsive to change, because it is able to detect an effect size of 0.2 to 0.3 in studies that compare an intervention group to a control group (33).

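### For the continuous outcomes, taking the group-by-time interaction as the effect is valid but gives away precision that prespecified adjustment for each outcome's own baseline would recover at no cost

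*Protocol*

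**What the plan says.** The Data analysis section of the protocol names the model terms: "In models, effects for group (intervention and control), time (baseline and 2-month follow-up) and group-by-time interaction will be included". It then names the effect measure: "The effect of the shared decision making aids on health outcomes will then be estimated by the interaction term between the group and time". Within-patient correlation is handled as follows: "generalized estimating equations will be used in order to take repeated measures into account". Annexe 1, Table 6 repeats this model for every outcome, with a normal distribution and identity link for the continuous ones, and reports the p-value of the interaction term.

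Each outcome has exactly two measurements. For decisional conflict, for example: "The questionnaire will be filled at baseline and after a 2-month follow-up". Under Evaluation of the aids, the baseline questionnaires are completed before the patient receives the randomisation envelope.

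Other covariates enter only if they are unevenly distributed between groups or change the effect measure by more than 10%. The list contains asthma knowledge, age, body mass index, atopy, environmental triggers and respiratory infections. It does not contain the baseline values of decisional conflict, compliance or asthma control. Baseline asthma knowledge is listed, but as a predictor of the other outcomes.

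**The concern.** With two visits, an identity link and a free group effect at baseline, the interaction subtracts the observed baseline difference in full from the 2-month difference. Because baseline precedes allocation, the true baseline difference is zero. What is subtracted is therefore chance variation, and its weight of one is larger than the correlation between visits warrants. Adjusting for baseline uses the weight that the data support.

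What is at stake is the width of the confidence intervals and the power for both primary outcomes and the continuous secondary outcomes. This matters even in a pilot. The protocol tests at the two-sided 5% level, says under Sample size that more patients may be enrolled to reach sufficient power, and under Research Utility links significant results to possible implementation. Precision that needs no further patients should be taken first.

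**Working it through.** **Inputs**

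- Sample size: "Since the study is a pilot, 50 patients are intended to be recruited to participate in the randomized control trial" (Sample size). The number rests on feasibility. No formula, power, effect size or standard deviation stands behind it, so there is no figure of the plan to reproduce.
- Allocation: no ratio is stated. There are two groups, and "Blocks of four will be used" (Randomization, sequence generation). I assume 1:1, taken as 25 per arm.
- Alpha: two-sided 0.05 (Data analysis). The 80% power below is only an illustration.
- rho, the correlation between baseline and 2 months: not given. It is an assumption, shown from 0.3 to 0.9.
- Equal standard deviations at both visits and complete data are assumed.

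**Step 1. What the interaction estimates.** In simulated complete data with 25 per arm, the GEE interaction equalled the difference in mean change exactly (−0.2573 in both forms in one dataset, 0.1707 in both in another).

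**Step 2. Variances per patient, in units of SD².**

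- Change score (the interaction): 2(1 − rho).
- ANCOVA on the 2-month value: 1 − rho².
- Ratio, ANCOVA to interaction: (1 − rho²) / [2(1 − rho)] = (1 + rho)/2.

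**Step 3. Small-sample cost.** ANCOVA also estimates a slope. With 50 patients this multiplies its variance by about 1 + 1/46 = 1.022.

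**Step 4. Results.** Corrected ratio R = 1.022 × (1 + rho)/2. Equivalent sample = 50/R. Interval narrowing = 1 − √R. The detectable difference at 80% power starts from the two-sample t-test value of 0.809 SD at 25 per arm, times √[2(1 − rho)] for the interaction, and times a further √R for ANCOVA.

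| rho (assumed) | (1+rho)/2 | R | 50 patients under ANCOVA are worth | Interval narrower by | Detectable difference in SD, planned / ANCOVA |
|---|---|---|---|---|---|
| 0.3 | 0.65 | 0.664 | 75 | 19% | 0.96 / 0.78 |
| 0.5 | 0.75 | 0.766 | 65 | 12% | 0.81 / 0.71 |
| 0.7 | 0.85 | 0.868 | 58 | 7% | 0.63 / 0.58 |
| 0.8 | 0.90 | 0.920 | 54 | 4% | 0.51 / 0.49 |
| 0.9 | 0.95 | 0.971 | 52 | 1.5% | 0.36 / 0.36 |

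Without the slope cost, the ANCOVA figure at rho 0.5 would be 0.809 × √0.75 = 0.70.

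Simulation of 8,000 trials per value of rho gave variance ratios (interaction to ANCOVA) of 1.52, 1.28, 1.16, 1.09 and 1.02. Their inverses are 0.66, 0.78, 0.86, 0.92 and 0.98, in line with R.

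**Step 5. Two boundaries.** Setting R = 1 gives rho = 2 × 46/47 − 1 = 0.957, so the gain vanishes near rho 0.96. At the other end, 2(1 − rho) exceeds 1 when rho is below 0.5. There the planned estimate is less precise than comparing 2-month means with no use of baseline (at rho 0.3, variance 1.40 against 1.00).

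**Step 6. Does the covariate rule help?** Adding a time-fixed baseline covariate as a main effect to the planned model left the interaction and its standard error unchanged in both simulated datasets (standard errors 0.2736 and 0.2703, with or without it). The ANCOVA standard errors in the same datasets (rho 0.5) were 0.227 and 0.234. The conditional rule, applied as main effects, therefore does not recover the loss.

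**The case against.** The strongest defence is that nothing here is an error. A GEE with group, time and their interaction is a recognised, internally consistent pre-post analysis, and it is unbiased under randomisation. That stands. A reader might infer from the mention of baseline differences that the planned estimate is biased, but the documents do not support this. Over-correction arises only conditionally, given a chance imbalance, and averages out over randomisations.

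The second defence is that the gain depends on a correlation that the protocol does not give. It describes its questionnaires as reproducible or supported by test-retest results, so a high rho cannot be excluded for some outcomes. This also stands, and it is why the range runs to 0.9. A reader might infer that ANCOVA wins at any correlation below 1. With 25 per arm it does not, because of the slope cost.

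Third, the change does not rescue a small pilot. At a true difference of 0.3 SD and rho 0.5, power rises only from 18% to 23% (normal approximation, slope cost ignored). That is correct. Nor has this been shown to be the largest precision gain open to the trial, since no alternatives were compared.

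Finally, a reader might infer from the naming of GEE and PROC GENMOD that uncorrected robust standard errors will make the tests too liberal. The protocol does not say which standard error or small-sample correction will be used, and that detail is commonly left to an analysis plan. It is no part of this point.

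**Conclusion.** The point holds as an avoidable loss of efficiency for the continuous outcomes, including both primary outcomes. The loss follows from text that the protocol fixes in Data analysis and Table 6, so it is not an omission.

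Over assumed rho from 0.3 to 0.7, the planned analysis makes 50 patients do work for which ANCOVA would need about 33 to 43 (50 × R). At 0.8 or above the loss is small. These figures assume 1:1 allocation, equal standard deviations and complete data. With missing 2-month values, the GEE interaction is no longer exactly the difference in mean change. The figures do not apply to binary compliance, where the log link makes the interaction a ratio of prevalence ratios.

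**What to change.** In Data analysis and Table 6, prespecify one of the following as the main analysis of each continuous outcome, whatever the observed balance:

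- a regression of the 2-month value on group plus the baseline value of the same outcome, with a t reference; or
- a repeated-measures model of both visits with a common baseline mean for the two arms and an unstructured covariance.

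The two give closely similar results with complete data. They differ when visit 2 is missed, because ANCOVA drops those patients, while the common-baseline model keeps their baseline records, as the planned GEE also does. The protocol expects some loss to follow-up (Bias section), so the choice should be stated. Keep the group-by-time GEE as a sensitivity analysis.

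The cost is a change of wording in one section and one table. Every baseline value needed is already collected, and no further patients or visits are required.

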**IG:** Intervention group (shared decision making) **CG:** Control group (usual care) **T1:** Baseline **T2:** 2-month follow-up

\* The effect of shared decision making aids on health outcomes will be estimated with their 95% confidence interval. The effect of the aids on asthma knowledge, decisional conflict, compliance with

controller/rescue/add-on pharmacotherapy, and asthma control will be expressed as means, since these variables are continuous. On the other hand, the effect of the aids on compliance with treatments (a binary variable) will be expressed as prevalence ratios. Both types of model will adjust for covariates, if a confounding variable results in a  $\geq 10\%$  change of the effect measure.

† P-value of the interaction term.

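### For binary compliance the plan calls the exponentiated group-by-time interaction a prevalence ratio, but it is a ratio of two prevalence ratios and is less precise than a baseline-adjusted 2-month ratio

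*Protocol*

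**What the plan says.** The protocol's section on compliance with treatments defines the binary variable strictly: to count as compliant, "patients need to meet all the 11 criteria". It is measured at baseline and at 2 months.

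The Data analysis section sets the model: "For compliance with pharmacotherapy, a binomial distribution and a log link will be used as this variable is expressed as a binary one". As to terms, "effects for group (intervention and control), time (baseline and 2-month follow-up) and group-by-time interaction will be included". The estimator is then fixed: "The effect of the shared decision making aids on health outcomes will then be estimated by the interaction term between the group and time". The next sentence gives the effect measures: "Mean differences (continuous variables) and prevalence ratios (dichotomous variable) have been" chosen. Generalised estimating equations handle the repeated measures.

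In Annexe 1, a footnote to Table 6 says that "the effect of the aids on compliance with treatments (a binary variable) will be expressed as prevalence ratios", with a 95% confidence interval, and a second footnote ties the p-value to the interaction term. Nowhere is the quantity called a ratio of prevalence ratios. No constraint of equal baseline prevalence is stated, and baseline compliance is not among the covariates listed for adjustment.

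**The concern.** The estimator and the effect measure are both fixed in the protocol, and they are different quantities. A prevalence ratio for the aids compares compliance under the aids with compliance under usual care at 2 months. The interaction compares the relative change from baseline in one arm with that in the other. Because the group main effect is left free, a chance baseline difference between two small arms enters the reported figure in full.

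Two things are at stake. A reader who takes the Table 6 effect at its label may misread its size. And the trial gives up precision on an outcome for which, with 50 patients, it has little to spare.

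**Working it through.** **Inputs.** From the protocol: log link; group, time and interaction terms; interaction as estimator; 50 patients; blocks of four. Assumed: 1:1 allocation, so 25 per arm (the ratio is not stated), and all prevalences and within-patient correlations (neither is given). The protocol has no figure of its own to reproduce here.

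**1. What the interaction estimates.** Write log p = b0 + b1·G + b2·T + b3·G·T, with G = 1 for the aids and T = 1 at 2 months.

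- Baseline prevalence ratio: exp(b1).
- 2-month prevalence ratio: exp(b1 + b3).
- Hence exp(b3) = (2-month prevalence ratio) / (baseline prevalence ratio).

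This equals the 2-month prevalence ratio only when exp(b1) = 1.

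**2. Illustration.** Baseline 4/25 (aids) versus 6/25 (usual care); 2 months 10/25 versus 7/25.

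- Baseline ratio: 4/6 = 0.67.
- 2-month ratio: 10/7 = 1.43.
- Planned estimate: 1.43/0.67 = 2.14.

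The shift can go either way. With 14 versus 11 compliant at 2 months (ratio 1.27), a baseline of 8 versus 12 gives 1.91, 12 versus 8 gives 0.85, and 10 versus 10 gives 1.27.

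**3. How often the two differ noticeably.** In simulation with 25 per arm, the observed baseline ratio fell outside 0.80 to 1.25 in about half of trials at 40% prevalence and about 66% at 20%. With no true effect, 40% prevalence and binary correlation 0.3 to 0.7, the interaction and the 2-month ratio pointed in opposite directions in 23 to 30% of trials.

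**4. Average behaviour.** With 40% at baseline and 60% versus 40% at 2 months (correlation 0.5), the mean log estimate was 0.421 for the interaction and 0.427 for the 2-month ratio. There is no material bias.

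**5. Precision against a baseline-adjusted 2-month ratio.** By the delta method, the variance of a log prevalence is v = (1 − p)/(n·p). With equal prevalence p in all four cells and binary correlation ρ:

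- Interaction: 4v(1 − ρ).
- Baseline-adjusted: 2v(1 − ρ²).
- Ratio of variances: 2/(1 + ρ), which exceeds 1 for every ρ below 1.

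At p = 0.40 and n = 25, v = 0.60/(25 × 0.40) = 0.06. At ρ = 0.5 the standard errors are √(4 × 0.06 × 0.5) = 0.346 and √(2 × 0.06 × 0.75) = 0.300.

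| ρ (p = 0.40 throughout) | SE, interaction | SE, baseline-adjusted | Variance ratio |
|---|---|---|---|
| 0 | 0.490 | 0.346 | 2.00 |
| 0.3 | 0.410 | 0.330 | 1.54 |
| 0.5 | 0.346 | 0.300 | 1.33 |
| 0.7 | 0.268 | 0.247 | 1.18 |
| 0.9 | 0.155 | 0.151 | 1.05 |

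If prevalence is 40% at baseline and 60% versus 40% at 2 months, the variance ratio runs from 2.38 (ρ = 0) to 1.39 (ρ = 0.9).

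Simulated SDs of the log estimate agree in direction. With 20% prevalence at baseline, 25% at 2 months and latent correlation 0.6 (binary correlation about 0.38), they are about 0.71 for the interaction and 0.54 for the adjusted ratio; repeat runs were within about 0.02. With 40% prevalence and latent correlation 0.9, they are 0.29 and 0.27.

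**The case against.** The interaction is a valid test of the aids' effect, and under randomisation the expected baseline log ratio is zero. The example above was chosen to show the gap. Table 6 also lays out baseline and 2-month values for both arms, has its own interaction column and says that the p-value belongs to the interaction. A careful reader could therefore recover the 2-month ratio. Calling a difference in differences a mean difference is similar shorthand. The outcome is one secondary variable in a pilot, and compliance is also analysed as a continuous score. All of this stands and limits the weight of the point, but it does not make the label correct.

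A reader might also infer three stronger things that the documents do not support.

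- *That the planned estimate is systematically inflated.* It is not; see step 4.
- *That the interaction is always less precise than a plain 2-month ratio.* With equal prevalences that holds only below a binary correlation of about 0.5, and the order reverses above it. The protocol gives no correlation, so only the comparison with a baseline-adjusted ratio is safe.
- *That the unadjusted log-binomial model is prone to non-convergence.* With group, time and interaction it is saturated and reproduces the four observed proportions. Trouble needs an empty cell or added covariates. The strict 11-criteria definition makes empty cells conceivable, but no prevalence is given. With independent cells, the chance of at least one empty cell is 1 − (1 − 0.9^25)^4 = 25.8% if 10% comply, but only about 0.9% at 20% and 25%.

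**Conclusion.** The point holds as a mismatch between estimator and named effect measure, together with an avoidable loss of precision. The mismatch is algebraic and needs no assumption. The size of the loss does rest on assumptions: 25 per arm, and prevalences and correlations that the protocol does not supply. Across the delta-method scenarios, including one with 20% at baseline and 40% versus 20% at 2 months (variance ratio 2.45 at ρ = 0), the interaction's variance exceeded that of the baseline-adjusted ratio by about 5% to 145%. It was larger in every scenario tried. No primary conclusion is affected. The change is worth making because the reported size of this secondary effect depends on it and the repair is cheap.

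**What to change.** In the Data analysis section and in Table 6 with its footnotes, define the effect on binary compliance as the 2-month prevalence ratio of aids versus usual care. Estimate it in PROC GENMOD with a log link and baseline compliance as a covariate, and report the p-value and 95% confidence interval of that group effect. If the covariate-adjusted log-binomial model does not converge, Poisson with robust variance is a suitable fallback, although it does not solve an empty 2-month cell.

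If the interaction is kept as the estimator, label it a ratio of prevalence ratios in both places.

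The cost is a few lines of text. Baseline compliance is already collected and the SAS procedure is already planned.
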